### Sample size

We powered our study to detect a standardized mean difference *d* = 0.38 (or larger) on the central clinical outcome (suicidal behaviors) using a test for independent means at α = 0.05 (2-tailed) and power of (1-b) = 0.80 while considering the design effect of the cluster randomization with schools as the unit of randomization and students being nested within schools. The relevant parameters are (1) the intraclass correlation coefficient, rho; the mean cluster size, *m*; the coefficient of variation, *cv*, of the cluster sizes; and the minimally detectable effect size, *d*. Regarding the last parameter, we looked at the well-known SEYLE study [55], where 2764 pupils in 43 schools were randomized to a universal prevention consisting of a Youth Aware of Mental Health (YAM) program (comparable to our universal intervention) and compared to a control group of 2933 students in 40 schools. YAM was associated with a significant reduction in incident suicide attempts (OR = 0.45, *p* = 0.014) and a reduction in severe suicidal ideation (OR = 0.50, *p* = 0.025). In our study, we expect similar or better effects because in addition to the universal preventive module, we will also offer the safety net provided by the gatekeepers training in addition to early detection and referral for adolescent students at elevated risk of suicide. For screen-positive students, an additional indicated preventive module will be offered. Nonetheless, we conservatively assume that the effectiveness of our integrated multi-component intervention will be of equal effectiveness as the YAM program. The OR of 0.50 translates into a standardized mean difference, *d*, of 0.38 when the outcome is measured on a continuous scale, as we will do [56]. The mean cluster size of *m* = 215 will be based on student population in the previous year. In the last year, the smallest school had 74 students and the largest 340. Accordingly, it follows that coefficient of variation *cv* = 0.31 [57]. In the SEYLE study of Wasserman et al. [55], the intraclass correlation coefficient was estimated at rho = 0.01 for severe suicidal ideation. To obtain an estimate of the required sample size, we used Stata’s procedure to estimate sample size needed for an independent groups t-test in a cluster randomized trial [58]. The corresponding syntax of clustersampsi, samplesize mu1(0.00) mu2(0.38) sd1(1) sd2(1) rho(0.01) m(215) size_cv(0.31) indicated *n* = 645 per condition, or *n* = 1290 in both trial arms. We will also compensate for a maximum of 30% dropout, which implies that we will need to have 1290/(1–0.30) =1844 participants at baseline.

### Program modules

The multimodal stepped-prevention program comprises screening with subsequent clinical evaluation and/or referral; gatekeeper training (QPR) for mentors; universal prevention focusing on stigma reduction; and identifying adolescents who have elevated signs of the most important risk factor for suicidal behaviors, i.e., depression with subsequent indicated prevention for screen-positive adolescents. These integrated four modules will be compared to the control condition. Schools in the control condition will adhere to the usual curricula and students in these schools will have full access to usual care offered by the regional health services, e.g., the Municipal Health Services (GGD), Primary Care, and (specialized) Mental Health Care services. In the context of this trial, we will prioritize the wellbeing and safety of participating students, especially those at elevated risk for suicidal behaviors and/or depressive disorder. Therefore, the screening and gatekeeper intervention will also be available to the control group. Consequently, the comparison condition will not exactly be “care as usual”; instead, it is described as “enhanced usual care” to guarantee the wellbeing and safety of participating students.

#### I. Screening

All students in their second year of secondary school (i.e., 8th grade in US), from vocational up to pre-university levels, will be screened for suicidal behaviors and depressive symptoms using the Questionnaire assessing Suicide and Self Injury (in Dutch: Vragenlijst over Zelfdoding en Zelfbeschadiging; VOZZ) [59] and the Childhood Depression Inventory 2 (CDI-2) [60]. The screening will be part of a larger health survey conducted by the health services of the school (in Dutch: GGD). Adolescents identified at risk for suicide are seen within 48 h by the health service of school (in Dutch: GGD). Parents of children identified as at risk for suicide by the mental health service of school will be informed. In accordance with parents, the adolescents will be referred to specialized mental health care, if deemed necessary by the health service of school, and will be excluded from the indicated intervention module. Adolescents who have been referred to specialized mental health care will also be approached to complete the same set of questionnaires as the children in the experimental and control condition to examine the effect of the screening and to monitor their mental health.

#### II. Gatekeeper training

All mentors of participating adolescents will be used as gatekeepers and trained to recognize suicidal behaviors, learn to initiate conversations after recognizing suicidal behaviors in a student, and learn to refer a student effectively and correctly, if deemed necessary. This training will be based on the Question, Persuade, and Refer (QPR) gatekeeper training [61]. Gatekeepers who will complete the QPR will show increased knowledge of suicide prevention, self-reported skills, competencies, and efficacy [42, 43]. Further information on the content, background, and structure of the online program is provided through an open-access protocol paper [62].

#### III. Universal prevention

The third module that will be evaluated is ‘Moving Stories’, which will be offered to all participating students in the experimental condition. The goal of ‘Moving Stories’ is to increase students’ mental health literacy (i.e., knowledge of depressive symptoms, effective strategies for dealing with depressive symptoms, and help-seeking strategies) and decrease depression stigma. It consists of an introduction presented by a researcher and the students’ school mentor, a serious game, and a debriefing by either an experiential expert only or a mental health professional in combination with a filmed experiential expert trained in the program with support from the students’ school mentor and a researcher at school. The game consists of five sessions, approximately 10–15 min per day. In a virtual house, adolescents will be asked to discover useful strategies to help a girl, Lisa, who is showing signs of depression. They can complete five actions each day and earn points with these actions. More points represent more trust between Lisa and the player, and this enables the players to call in help from an adult. For example, students can make drinks or food, call her parents, or clean the house, among other things. To identify useful strategies, they can talk to the girl in the house. Students will receive feedback on their actions during the day.

#### IV. Indicated prevention

The fourth module, namely the indicated module, is ‘OVK2.0’, which will only be offered to screen-positive students (CDI-2 ≥ 14) in the experimental condition. It consists of 8 lessons of 60 min each. The intervention is based on the principles of cognitive behavioral therapy (CBT) and is a modified version of the OVK-program that was based on the PRP. It only includes the lessons that are based on the CBT techniques, as they were considered most effective [50]. Details about the content of the program are described extensively elsewhere [49]. It will be delivered by two trainers, a licensed psychologist who is a school staff member and a co-trainer who is a licensed member of a (mental) health institution. The trainers underwent an extensive 3-day training program in the necessary skills, such as CBT and its theoretical background, a training manual, and the intervention protocol.

### Study outcome measures

For an elaborate overview of study outcome measures, see Table 1.

**Table 1 Tab1:** Overview of assessments

	Screening	T0	T1	T2	T3	T4	T5
Adolescent							
Suicide risk (VOZZ-Screen)	X						
Suicidal behaviors (VOZZ)		X	X	X	X	X	X
Depressive symptoms (CDI-2)	X	X	X	X	X	X	X
Clinical depression (ADIS-C)						X	
Stigma (DSS)		X	X	X	X	X	X
Social connectedness		X	X	X	X	X	X
Mastery (PMS)		X	X	X	X	X	X
Worry (PSWQ)		X	X	X	X	X	X
Perfectionism (MPS)		X					
Life events (TP)		X	X	X	X	X	X
School							
Academic grades	X	X	X	X	X	X	X
Drop-out rates	X	X	X	X	X	X	X
Non-attendance	X	X	X	X	X	X	X
Truancy	X	X	X	X	X	X	X

### Screening

To assess suicide risk, adolescents will be screened using the VOZZ [59] and item 8 of the CDI-2 [60]. The VOZZ-Screen is a self-report questionnaire comprising 10 items. This questionnaire contains ten questions assessing thoughts and actions about life, self-harm, suicide, and suicidal ideations in the past 7 days. Items assessing the participant’s life are rated on a 5-point scale from 1 (I totally agree) to 5 (I totally disagree) (e.g., ‘I feel worthless’). Items about self-harm and suicide are rated on a 5-point scale from 1 (never) to 5 (very often) (e.g., ‘I have harmed myself deliberately’). Items about suicidal ideation in the past 7 days are rated on a 5-point scale from 1 (never) to 5 (every day) (e.g., ‘I thought that suicide would be a solution for my problems’). A score of ≥23 requires subsequent action in the form of a personal conversation to assess acute suicide risk. The CDI-2 is also a self-report questionnaire comprising 28 items assessing depressive symptoms, each consisting of three statements rated in severity from 0 to 2 (e.g., ‘I don’t feel alone’ = 0 ‘I often feel alone’ = 1, ‘I always feel alone’ = 2). Item 8 of the CDI-2 measures the presence of suicidal ideation on a three-point scale (0 = I don’t think about ending my life, 1 = I think about ending my life, but I would never do it, 2 = I want to end my life). The CDI-2 will be used for screening purposes in accordance with the Dutch clinical guidelines for depression among youth [63].

### Primary outcome measure

*Suicidal behaviors* will be measured using the full VOZZ questionnaire [59]. This questionnaire contains 39 questions assessing thoughts and actions about life, self-harm, suicide, and suicidal ideations in the past 7 days. It is a combination of the VOZZ-Screen and 29 additional items. Scoring is the same as described earlier for the VOZZ-Screen. A score of 86 or above indicates high risk of suicide. The reliability was high in an adolescent sample (Cronbach’s α = 0.91; *r* = 0.82) [59].

### Secondary outcome measures

*Depressive symptoms* in children and adolescents will also be measured with the CDI-2 [60], as described in previous section.

*Clinical depression* will be measured by the Anxiety Disorder Interview Schedule for Children (ADIS-C; [54]) during a clinical interview. It is a semi-structured diagnostic interview that is used to diagnose anxiety and comorbidity. All interviews will be administered by a qualified psychologist.

*Stigma* will be measured using the Depression Stigma Scale (DSS) [64]. It measures personal depression stigma and perceived depression stigma. Both scales have a good internal consistency (Perceived Scale: Cronbach’s α = 0.82; Personal Scale: Cronbach’s α = 0.78) [64]. The Personal Stigma Subscale measures stigma in the respondents’ own attitudes towards depression. The Perceived Stigma Subscale measures the respondent’s perception about the attitudes of others towards depression. Both subscales consist of 6 items and responses to each item are measured on a five-point scale (ranging from 0 ‘strongly disagree’ to 4 ‘strongly agree’). Higher scores indicate higher levels of depression stigma.

*Social connectedness* will be measured using a single item construct. Research has shown that a single item measure of social identification is reliable [65]. As the construct has not yet been used in this age group, we have included three extra items for (potential) increased reliability of the construct. Social connectedness will be measured for the class, the ‘OVK’-group, and school. Items are rated on a scale of 1 (“strongly disagree”) to 7 (“strongly agree”).

*Mastery* will be measured with the Pearlin Mastery Scale (PMS; [66]), which consists of 7 items. It measures perceived control of one’s life. Each item has the following response options: (1) Strongly Disagree (2) Disagree (3) Agree (4) Strongly Agree. It is a widely used measurement of mastery, with a higher score indicating higher mastery. Previous studies have found good reliability of the PMS (Cronbach’s α = 0.78) [67].

*Worry* will be assessed with the Penn State Worry Questionnaire for children (PSWQ-C; [68]). It is widely used in both research and clinical practice to reliably assess worry in both clinical and non-clinical samples and adolescents [69]. The Dutch version has also been shown to be reliable for assessing worry in children [70]. The PSWQ-C consists of 14 items. Each item is rated on a scale of 0 (“never”) to 3 (“always”). Higher scores indicate higher levels of worry.

*Perfectionism* will be assessed using the Frost Multidimensional Perfectionism Scale (FMPS) [71]. It consists of 35 items and has good internal reliability (Cronbach’s α = 0.90) [71]. Each item is rated on a scale of 1 (not true at all) to 5 (completely true), with a higher score indicating more levels of perfectionism. It measures six subscales, namely concern over mistakes, personal standards, parent expectations, parental criticism, doubting of actions and organization. A higher score indicates greater levels of perfectionism.

*Life events* will be recorded and assessed using The Top Problems (TP) [72] measure. It assesses life events that participants consider the most important at that time. Participants are asked to list three problems about which they are most concerned. Furthermore, they are also asked to rate the severity of all three problems separately on a scale from 0 (not at all) to 10 (very, very much). As such, it not only measures actual life events, but also accounts for personal salience of life events, as opposed to most life events measures.

*Hopelessness* will be assessed using the VOZZ. Previous studies have found that correlations between the hopelessness scale by Beck and the VOZZ were 0.79 and 0.58 [59]. The items 3, 4, 21, 28, and 31 of the VOZZ, which were established in accordance with the first author of the VOZZ, will be used to assess hopelessness.

*School-related factors,* such as academic grades, drop-outs, non-attendance, and truancy will be obtained in collaboration with the schools.

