### Design

The presented study is designed as a non-blinded cluster-randomized controlled trial with two parallel groups (experimental and control) to evaluate the effectiveness of a multimodal stepped-prevention program relative to (enhanced) usual care. The participants in the experimental condition will receive all four modules of the multimodal stepped-prevention program, whereas participants in the control condition will receive modules 1 and 2. Randomization will be conducted at school level (to be more precise: at the level of school location because one school can have annexes at multiple locations) to avoid contamination. An independent statistician will randomly assign the participating school locations to the intervention or control condition using random.org. Furthermore, randomization will be stratified for (1) education level (vocational training as one category, in Dutch: VMBO; and higher education / pre-university as the other category, in Dutch: HAVO/VWO) because school type is a relevant prognostic predictor of outcome [54]. Like most psychological and public health interventions, blinding of participants is not possible; therefore, it will not be attempted. The assessments will be conducted at baseline (T0), during the intervention phase after the third module (T1), at post-intervention (T2), at 6-month follow-up (T3), at 12-month follow-up (T4), and at 24-month follow-up (T5). The overall study design is shown in Fig. 1.

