### Strengths and limitations

One of the strengths of this study is that it will include the follow-up assessment of 24 months, providing the opportunity to evaluate the longer-term effects. Second, the multimodal stepped-prevention program will be implemented in all secondary schools in a rural region in The Netherlands, with a strong collaboration between schools’ and (mental) health organizations. A meta-analysis of Brunwasser and Garber [108] on the effectiveness of programs for the prevention of youth depression revealed the need to conduct studies in real-life conditions, like the one we are proposing. Third, the current study uses a between-schools design which minimizes contamination effects that might occur in a within-schools design. An additional strength of the study is that in contrast to the most RCT studies, we will focus not only on the effectiveness of the program, but also on the mediators of change (i.e., how the intervention works) and on the characteristics of the student population that may act moderators. This will shed light on how the intervention works and for whom it is effective.

Several limitations of this study must be noted. As we evaluate the effectiveness of the multimodal stepped-prevention program, no conclusions regarding the specific components of the program can be made. Additionally, we will not complete a clinical interview prior to the interventions (only at post measurement). Thus, it is possible that some adolescents meeting the diagnostic criteria of a full-fledged depression may be included in the study. For those, the intervention becomes the treatment rather than the prevention. However, since sub-threshold depression or minor depression is sometimes viewed as a clinical disorder (as is the case in the DSM-5), the current study might not be classified as the prevention of the imminent onset of a new disorder, but rather as the treatment of an existing disorder. Additionally, the study will be conducted in a specific region in The Netherlands, which may limit the generalizability of the results to other regions in The Netherlands.

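### The reason given for not blinding covers participants only, and nothing masks the psychologists who make the ADIS-C depression diagnosis, the one rater-judged outcome

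*Protocol article*

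**What the plan says.** The Protocol article settles blinding in its Design section. The trial is "designed as a non-blinded cluster-randomized controlled trial with two parallel groups", and the reason follows: "Like most psychological and public health interventions, blinding of participants is not possible; therefore, it will not be attempted". The reason is about participants; assessors are not mentioned.

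Under Secondary outcome measures, clinical depression "will be measured by the Anxiety Disorder Interview Schedule for Children". On the instrument: "It is a semi-structured diagnostic interview that is used to diagnose anxiety and comorbidity". On the rater: "All interviews will be administered by a qualified psychologist". Nothing is said about what the interviewer knows of the school's arm, or about independence from program delivery.

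Two other places bear on the point. The Interim analysis section gives that analysis to an independent statistician who is blinded to allocation. Strengths and limitations says that "we will not complete a clinical interview prior to the interventions (only at post measurement", so there is no diagnostic interview before the program starts.

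**The concern.** That participants cannot be blinded is a sound reason for leaving participants unblinded. It is no reason for leaving an outcome assessor unmasked, yet the label attached to the trial makes no distinction between the two. Where outcomes are self-reported, the distinction has no practical effect, because the person who reports is the participant. It matters for an outcome that a psychologist judges in a semi-structured interview, where borderline cases depend on probing and interpretation.

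An interviewer who knows that a school had the full program may score borderline cases differently, in either direction. With no interview before the intervention, a between-arm difference in diagnosis cannot be set against baseline diagnoses. Sensitivity analysis could bound differential misclassification under assumed error rates but could not remove it. What is at stake is the credibility of one secondary outcome.

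**Working it through.** The plan gives no figure on this point, neither an expected ADIS-C prevalence nor a rater error rate, so there is nothing to reproduce. The check is mainly a comparison of sections.

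**Which outcomes depend on a study rater?**
- Suicidal behaviors: the full VOZZ is a questionnaire, scored in the same way as the VOZZ-Screen, which the Screening section calls self-report. No rater.
- Depressive symptoms: the CDI-2 is self-report. No rater.
- Stigma, social connectedness, mastery, worry, perfectionism and life events: items rated, or problems listed, by the adolescent. Hopelessness uses VOZZ items. No rater.
- Grades, drop-out, non-attendance and truancy: obtained with the schools, not judged by a study assessor.
- Clinical depression: ADIS-C, judged by a psychologist.

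Only the last could gain from interviewer masking.

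**Does the reason for no blinding reach that rater?** No. It concerns participants. The Interim analysis section masks another non-participant role, so the article itself treats masking of such roles as possible.

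**Illustration of size (all rates assumed).** Suppose equal true prevalence in both arms, hence a true odds ratio of 1, no false positives, and a fraction f of true cases missed in the experimental arm only. The apparent prevalence there is p(1 − f), and

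OR = [p(1 − f) / (1 − p(1 − f))] ÷ [p / (1 − p)].

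| p | f | Apparent prevalence | Odds ratio |
|---|---|---|---|
| 0.05 | 10% | 0.045 | (0.045/0.955) ÷ (0.05/0.95) = 0.895 |
| 0.05 | 20% | 0.040 | (0.040/0.960) ÷ (0.05/0.95) = 0.792 |
| 0.10 | 10% | 0.090 | (0.090/0.910) ÷ (0.10/0.90) = 0.890 |
| 0.10 | 20% | 0.080 | (0.080/0.920) ÷ (0.10/0.90) = 0.783 |

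The range is about 0.90 to 0.78.

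**Sensitivity to the assumptions.** Let sensitivity be Se and specificity Sp, so that apparent prevalence is p·Se + (1 − p)(1 − Sp). Take p from 3% to 8%.
- Sp 98% in both arms, Se 85% (control) against 75% (experimental), p = 3%: 0.0449 against 0.0419, odds ratio 0.93.
- The same Sp, Se 90% against 70%, p = 8%: 0.0904 against 0.0744, odds ratio 0.81.
- If Sp also differs (97% control, 99% experimental), these pairs of sensitivities give about 0.53 to 0.70.

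The figures move widely with the assumptions, and over-calling in the experimental arm would push the odds ratio above 1. They show only that moderate differential error can produce a visible shift.

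**The case against.** The strongest reply is that the article is a condensed account. Who interviews, how interviewers are trained and what they are told are details that a full protocol may hold. The sentence that says blinding will not be attempted refers to participants and is correct as it stands. This has force: the point is that the stated rationale stops short of the assessors, not that the article contains a false statement.

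Several stronger readings are tempting, and the article does not support them.
- *That interviewers will know the arm.* A reader might infer this from the non-blinded label. The label stands once, in Design, and the interim statistician is blinded, so it does not describe every role.
- *That the people delivering the program also do the interviews.* OVK2.0 is led by a psychologist on the school staff with a co-trainer from a (mental) health institution. Moving Stories involves a researcher, the mentor, and an experiential expert or a mental health professional. Nothing links any of them to the ADIS-C, and a shared professional title is not evidence of overlap.
- *That masking would remove the bias.* The schools lie in one region, allocation is by school location, and the sample size implies 645/215 = 3 schools of average size per arm before the dropout allowance. An interviewer who knows the school may well learn its arm.
- *That the trial's main conclusions are at risk.* The primary outcome is the VOZZ, and the Analysis section names only the CDI-2 as the secondary outcome. It describes no between-arm comparison of the ADIS-C.

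It is also fair to say that the main illustrated shift is small beside sampling error. With 645 interviewed per arm and clustering ignored, the standard error of the log odds ratio at 5% prevalence is √(2/(645 × 0.05 × 0.95)) = 0.256, so 95% limits around 1 are about 0.61 to 1.65. At 10% it is √(2/(645 × 0.10 × 0.90)) = 0.186, with limits of about 0.70 to 1.44. The shift to 0.90 or 0.78 lies inside both. That limits the weight of the point but does not answer it, since bias moves the estimate whatever its precision.

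**Conclusion.** The point holds in a limited form. The article gives a reason for no blinding that applies to participants and leaves unaddressed the one outcome judged by a study rater, where masking of non-participants would be useful. It is a desirable improvement, confined to a secondary outcome that carries little weight in the article's analysis.

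The size is unknown. An odds ratio of about 0.90 to 0.78 under no true effect rests on assumed prevalence (5% to 10%), assumed under-calling (10% to 20% of cases) and error in one arm and one direction only. The conclusion does not depend on these figures. It rests on the wording of the Design section, on the nature of the interview, and on the premise that at least partial masking is practicable, which is reasonable but not shown.

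**What to change.** In Design and in Secondary outcome measures, state that:
- ADIS-C interviewers are not told the school's allocation;
- they did not deliver module III or IV in the school where they interview;
- students are asked before the interview not to mention the program;
- interviewers record any unmasking.

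Then describe the trial as open to participants with masked diagnostic interviewers. If masking cannot be arranged, say why.

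The cost is a constraint on scheduling interviewers who are already planned, one instruction to students, and one item on the interview form. Sample size, power and alpha stay as they are. Masking will be incomplete, because a known school location can reveal the arm, and the record of unmasking lets readers judge how far it held.

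While these sections are open, reconcile the timing of the interview: Table 1 places the ADIS-C at T4 (12 months), whereas Strengths and limitations places it at post measurement, and Design labels post-intervention as T2.

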#### Analysis of effect mediation

It is important to determine the mediators that affect the intervention effect. This helps determine whether the intervention works through expected mechanisms and which improvements could be effective. Mediation analyses will be performed in Mplus [73], where indirect effects will be tested with bootstrap methods. More specifically, we will test whether (1) mastery, (2) stigma, (3) worry, (4) top problems, (5) social connectedness, and (6) hopelessness will mediate the intervention effect on VOZZ suicidal behaviors and / or CDI-2 depression.

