## Discussion

The present study protocol describes a RCT on the effect of a multimodal school-based prevention program on suicidal behaviors in adolescents. The primary aim is to investigate whether the multimodal school-based program results in a clinically significant reduction of suicidal behaviors and depressive symptom levels in secondary school students compared to ‘enhanced’ care as usual. The secondary aim is the evaluate pathways that transmit the intervention effect on the primary outcome: (a change in) stigma, social connectedness, mastery (i.e., level of internal locus of control), worry, hopelessness, and number of self-reported major problems. Another secondary aim is to identify modifying factors that increase or decrease the intervention’s effectiveness: baseline level op depressive symptoms, baseline level of suicidal behaviors, perfectionism, gender, mastery, and ethnic descent / cultural background.

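### The hopelessness mediator consists of five items of its own outcome, the 39-item VOZZ, so the mediator-outcome path in that one model is inflated by item overlap

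*Protocol article*

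**What the plan says.** Three statements in the protocol article together define this analysis.

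- **Primary outcome measure.** Suicidal behaviors "will be measured using the full VOZZ questionnaire". It has 39 questions and is described thus: "It is a combination of the VOZZ-Screen and 29 additional items".
- **Secondary outcome measures, Hopelessness.** There is no separate instrument. "The items 3, 4, 21, 28, and 31 of the VOZZ" are the items that "will be used to assess hopelessness", and Table 1 lists no other hopelessness measure.
- **Analysis of effect mediation.** Indirect effects are to be tested by bootstrap in Mplus. The sixth hypothesis is stated as "6) hopelessness will mediate the intervention effect on VOZZ suicidal behaviors", with CDI-2 depression as the other possible outcome.

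No section takes the five items out of the VOZZ score for this model. The wave at which mediator and outcome are measured is not stated.

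**The concern.** A mediation model asks whether a change in one thing carries the intervention's effect to another. Here the first thing is a piece of the second. Part of the association between mediator and outcome is then arithmetic, and the data cannot show otherwise. If the intervention shifts the five items for any reason, the VOZZ model credits hopelessness with a share of the effect, whether or not hopelessness has any bearing on the remaining 34 items.

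Mediation is a stated secondary aim and is listed among the study's strengths. The Analysis of effect mediation section says its purpose is to learn whether the intervention works through the expected mechanisms. At stake is whether the hopelessness result on the VOZZ can be read that way.

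**Working it through.** **Inputs from the protocol article**
- Outcome: 10 screen items + 29 further items = 39, which agrees with the stated 39.
- Mediator: 5 of those items, so 5/39 = 12.8% of the outcome; 39 − 5 = 34 remain.
- Cronbach's alpha of the VOZZ: 0.91.

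**Assumptions not in the article**
- The VOZZ score and the hopelessness score are plain sums of items.
- Items have equal variance (set to 1) and equal inter-item correlation r.

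**Step 1: the identity.** Let H be the sum of the five items, R the sum of the other 34, and T = H + R. In a linear model of the outcome on treatment and H from the same wave, least squares is additive in the response. The regression of H on treatment and H has coefficient 1 on H and 0 on treatment. Hence
- b(T) = b(R) + 1;
- with a the treatment effect on H, indirect effect a·b(T) = a·b(R) + a.

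If H is unrelated to R, then b(R) = 0 and the indirect effect on T is still a. This step needs only the sum-score and same-wave assumptions.

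**Step 2: size at the stated reliability.**
- r = 0.91 / (39 − 38 × 0.91) = 0.91 / 4.42 = 0.206. Check: 39 × 0.206 / (1 + 38 × 0.206) = 0.91.
- Var(H) = 5 + 20r = 9.12; Cov(H, R) = 5 × 34 × r = 35.0.
- b(R) = 35.0 / 9.12 = 3.84; b(T) = 4.84.
- Var(R) = 34 + 34 × 33 × r = 265; corr(H, R) = 35.0 / √(9.12 × 265) = 0.71.
- Var(T) = 39 + 39 × 38 × r = 344; corr(H, T) = (35.0 + 9.12) / √(9.12 × 344) = 0.79.
- If the treatment effect is spread evenly over the items, the proportion mediated is 5 × 4.84 / 39 = 0.62 on 39 items and 5 × 3.84 / 34 = 0.56 on 34 items.

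**Step 3: the limiting case r = 0.** Here hopelessness has no relation to the rest of the scale. The part-whole correlation is √(5/39) = 0.36, against 0 with the other 34 items.

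**Step 4: simulation.** n = 1290, 300 runs per setting. Where the effect is even, its total size is d = 0.38. Clustering was ignored, and a joint-significance test stood in for the bootstrap.

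| Setting | Outcome | b | Proportion mediated | Indirect effect significant |
|---|---|---|---|---|
| r = 0, even effect | 39 items | 1.00 | 12% | 64% |
| r = 0, even effect | 34 items | 0.00 | 0% | 3% |
| r = 0.206, even effect | 39 items | 4.84 | 62% | 100% |
| r = 0.206, even effect | 34 items | 3.84 | 56% | 100% |
| r = 0, no effect on any item | 39 items | 1.00 | not meaningful | 6% |

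**Step 5: mediator from an earlier wave.** The excess of 1 is replaced by the regression of the later five items on the same five items earlier. With otherwise uncorrelated items and assumed item stability of 0.3, 0.5 and 0.8, simulated b on the 39-item outcome was 0.30, 0.51 and 0.80. On the 34-item outcome it was about 0 each time. Lagging the mediator reduces the overlap effect but does not remove it.

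**The case against.** **The indirect effect is not guaranteed.** A reader might infer that mediation is built in by construction. It is not. An indirect effect also needs the intervention to move the five items, and the overlap does nothing to that path. With no treatment effect on any item, the joint test was positive in about 6% of runs. This part of the objection stands and limits the point to the mediator-outcome path.

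**The striking figures come from an unrealistic case.** The contrast of b = 1.00 against 0.00 supposes that hopelessness is unrelated to the rest of the VOZZ. The article's alpha of 0.91 speaks against that, as do its reported correlations of 0.79 and 0.58 between the VOZZ and a separate hopelessness scale. (That 0.79 agrees with the computed part-whole value by coincidence.) At alpha 0.91 most of the association survives removal of the items. This stands too: the inflation is modest.

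**Timing and scoring are usually left to the analysis plan.** That is fair for the wave, which is therefore not criticized here. It does not answer the overlap, because the article itself fixes the item set, the outcome score and the hypothesis. An earlier-wave mediator alone would not resolve the conflict.

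**Other mediators.** A reader might also infer that two further mediators cannot work as defined. The article does not support this.
- The Discussion speaks of the "number of self-reported major problems", while under Life events "Participants are asked to list three problems about which they are most concerned", which would leave a count little room to vary. But the mediation section names top problems, not their number. A 0–10 severity is recorded for each problem, and the stated rationale is experienced disruptiveness. The word is loose in one summary sentence only.
- An OVK group exists only for some students in the experimental arm. But "Social connectedness will be measured for the class" and for the school as well, and both apply in each arm. Nothing says that the OVK-group items enter the mediator.

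**Conclusion.** The point holds in limited form. As written, the plan regresses the 39-item VOZZ on five of its own items, so the hopelessness result on that outcome cannot be read cleanly as a mechanism. With same-wave sum scores, the excess in the coefficient is exactly 1 per raw point, and the excess in the indirect effect is the whole treatment-to-hopelessness path. With a lagged mediator, the excess is the items' own stability.

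At the stated alpha, b is 4.84 against 3.84, the correlation 0.79 against 0.71, and the proportion mediated 0.62 against 0.56 under an evenly spread effect. The alpha-based figures rest on equal inter-item correlations, which the article does not give. The overlap would weigh more if the five items were less related to the rest of the scale than that assumption implies.

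Severity is moderate. One of six mediators is affected, for one of two outcomes. The CDI-2 shares no items with this mediator, so that mediation stands, and neither the primary VOZZ analysis nor the sample size is touched.

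**What to change.** State, before outcome data are examined, that in the hopelessness mediation model only, the outcome is the VOZZ without items 3, 4, 21, 28 and 31 (34 items). If that model carries a baseline VOZZ covariate, it should be the same 34-item score. The alternative is to test hopelessness as a mediator of the CDI-2 effect only.

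If the authors also wish to report the model on the full VOZZ, it should be labeled as containing the overlap and shown beside the 34-item result.

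The cost is a sentence or two of wording. The VOZZ is already scheduled at T0 to T5, so no new data are needed and the primary outcome stays as it is. The downside is that the 34-item score differs slightly from the validated total: the published alpha and the cut-off of 86 do not carry over to it. That matters little for a score used in one mediation model.
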